### Intervention

#### Ketogenic diet

Patients assigned to the ketogenic diet group will be hospitalized in the tertiary epilepsy center for 1 week. During this week the ketogenic diet is introduced by a dietician. The anti-epileptic drugs the children and adolescents use at the time of inclusion in the study will be continued without changes during the study (except when medically indicated). The initial calorie prescription for the ketogenic diet is based on an average between the pre-diet intake and the recommendations for energy requirements, taking into account current and previous weight and height, recommended caloric requirements and levels of physical activity. The dietician will decide together with the parents whether the classical diet or the medium-chain triglyceride (MCT) diet is introduced. Sometimes the MCT diet is not possible and the classical ketogenic diet (3:1 or 4:1 ratio) is advised. Children with a PEG/tube feed are also treated with the ketogenic diet. The diet is then adjusted to a fluid version. It is possible to decrease the titration of anti-epileptic drugs in responders from six months after the initiation of the ketogenic diet.

#### Usual care

Patients randomized to usual care will continue to take their anti-epileptic drugs and no changes will be made to the anti-epileptic drugs treatment. Since a ketogenic diet is a treatment of last resort, the children in the usual care group will also receive a ketogenic diet after a delay of four months. The controls will be treated and monitored according to good clinical practice; however, this is not part of our proposed study.

#### Timeline of the study

The timeline of the study is shown in Figure 2. Patients in the intervention group will visit the multidisciplinary team (nurse practitioner, dietician, paediatrician and neurologist) at time points T0 (at baseline), T1 (during admission), T2 (6 weeks after admission), T3 (4 months after admission), FU1 (3 months follow-up), FU2 (6 months follow-up), FU3 (9 months follow-up), and FU4 (12 months follow-up). At T0, T3, and FU4 a neurocognitive assessment will take place. An overview of measurements per time point is shown in Table 1. Patients in the intervention group will be asked to follow the diet during the complete study period and during follow-up, 16 months in total.

**Figure 2 F2:**
[figure not shown]
**Timeline of the study**. Note: T0 = baseline; T1 = Admission; T2 = 6 weeks after baseline period; T3 = 4 months after baseline period; FU1 = 3 months follow-up; FU2 = 6 months follow-up; FU3 = 9 months follow-up; FU12 = 12 months follow-up.

**Table 1 T1:** Overview of measurements per time point

Measurement	T0	T1*	T2	T3	FU1*	FU2*	FU3*	FU4*
Demographic characteristics	x							

Clinical measurement	x	x	x	x	x	x	x	x

National Hospital Seizure severity scale	x	x	x	x	x	x	x	x

Side effects of Anti-Epileptic Drug	x	x	x	x	x	x	x	x

Credibility And Expectancy Questionnaire	x							

Peabody Picture Vocabulary test	x			x				x

Beery Developmental Visual-Motor Integration test	x			x				x

Fepsy computerized test	x			x				x

Kaufman Assessment Battery	x			x				x

Actigraphy	x			x				x

SEV Questionnaire	x			x				x

SDQ Questionnaire	x			x				x

POMS Questionnaire	x			x				x

The Personal Adjustment and Role Skills Scale	x			x				x

The Hague Restrictions in Childhood Epilepsy Scales	x			x				x

EuroQol	x			x				x

TAPQOL or TACQOL	x			x				x

Blood	x		x	x	x	x	x	x

Urine	x		x	x	x	x	x	x

Keton bodies measurement	x	x	x	x	x	x	x	x

ECG	x			x	x	x	x	x

T0 = baseline; T1 = Admission; T2 = 6 weeks after baseline period; T3 = 4 months after baseline period; FU1 = 3 months follow-up; FU2 = 6 months follow-up; FU3 = 9 months follow-up; FU12 = 12 months follow-up; *= intervention group only.

Patients in the usual care group will visit the multidisciplinary team (nurse practitioner, paediatrician and neurologist) at time points T0, T2, and T3 and will have a neurocognitive assessment at T0 and T3. In case of drop-out, a visit with the multidisciplinary team and a neurocognitive assessment will take place.

### I) Effect evaluation

Several instruments will be used to assess the effects of the ketogenic diet on the primary outcome (seizure frequency) and on secondary outcomes (seizure severity, side effects, neurocognitive assessment and quality of life).

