**Methods/Design:**

In a RCT we will compare the ketogenic diet with usual care. Embedded in this RCT will be a trial-based and model-based economic evaluation, looking from a societal perspective at the cost-effectiveness and cost-utility of the ketogenic diet versus usual care. Fifty children and adolescents (aged 1-18) with intractable epilepsy will be screened for eligibility before randomization into the intervention or the usual care group. The primary outcome measure is the proportion of children with a 50% or more reduction in seizure frequency. Secondary outcomes include seizure severity, side effects/complaints, neurocognitive, socio-emotional functioning, and quality of life. Costs and productivity losses will be assessed continuously by a prospective diary and a retrospective questionnaire. Measurements will take place during consults at baseline, at 6 weeks and at 4 months after the baseline period, and 3, 6, 9 and 12 months follow-up after the 4 months consult.

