#### I) Effect evaluation

(1) What are the effects of the ketogenic diet in comparison with usual care with respect to changes in seizure frequency and seizure severity, side effects/complaints, neurocognitive, socio-emotional functioning, and quality of life?

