### Sample Size

A 50% reduction in seizure frequency is considered clinically relevant and is defined as success. Assuming a minimum detectable difference in success rate of 35% between the ketogenic diet group and usual care, and assuming that alpha = 5% and power = 80%, we need 22 children for each group. Taking dropouts into account, we need 50 children in total. A drop-out is defined as a child who drops out of the study before the first consultation with the neurologist; this is scheduled 6 weeks after initiating the KD or 6 weeks after randomization to usual care.

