#### Primary outcome

##### Seizure frequency

A seizure calendar is used to record seizures. Types of seizures are described and labelled in accordance with ILAE classification. The number and type of seizures are recorded on the dates they occur.

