### Analyses

#### I) Effect evaluation

Our primary (base-case) analyses will be performed according to the intention-to-treat principle, including data from all participants regardless of whether they received the intervention or not. For the analyses we will use SPSS statistical software. Respondents for whom at least 75% of the data per measurement instrument are available will be included in the analysis. Missing data on an item level will be handled using SPSS missing value regression analysis. Completely missing measurements will be handled using multiple imputation. Between-group differences in proportions (dichotomous variables) will be tested using the Chi-square test and between-group differences in means (continuous variables) will be tested using Student's t-test for independent samples. In addition, a multivariate regression analysis will be performed with the covariates of sex, age, severity of disease, duration of disease etc. The accuracy of the findings will be expressed in terms of 95% confidence intervals.

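### The outcome section labels the primary outcome only as seizure frequency, and seizure frequency as a continuous variable would get an unadjusted Student's t-test, which is inefficient for skewed counts

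*Protocol article*

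**What the plan says.** Four parts of the Protocol article bear on this.

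- **Primary outcome as a responder proportion.** Abstract, Methods/Design: "The primary outcome measure is the proportion of children with a 50% or more reduction in seizure frequency". Sample Size: "A 50% reduction in seizure frequency is considered clinically relevant and is defined as success". The trial is sized on that rate: "Assuming a minimum detectable difference in success rate of 35" percentage points.
- **Primary outcome as a bare label.** The outcome description under Effect evaluation speaks of the "primary outcome (seizure frequency" and closes the bracket there. The Seizure frequency subsection beneath it describes only the calendar: "The number and type of seizures are recorded on the dates they occur". No responder variable is derived there.
- **Research question.** Under Effect evaluation it asks about "changes in seizure frequency and seizure severity", among other domains.
- **Tests.** In the Analyses section, Effect evaluation, dichotomous variables get a chi-square test. For the rest, "between-group differences in means (continuous variables) will be tested using" an unpaired Student's t-test. An additional regression lists sex, age, disease severity and disease duration, and ends with an open et cetera. Baseline seizure frequency is not named.

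**The concern.** Seizure counts usually differ many-fold between children. A two-sample t-test on follow-up frequency, or on raw change, is then driven by the few children with the highest counts. It also leaves out the child's own baseline count, normally the best predictor of the later count. The trial already collects that baseline. The article foresees skewness for costs and plans a normality check and bootstrapping for them, but it names no comparable step for seizure frequency.

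At stake is the answer to the research question on change in seizure frequency. With about 22 children per arm, a real effect that shows in the responder analysis could be missed in the frequency analysis because of the test alone. The loose label adds a smaller problem: the section where a reader looks up the primary outcome does not state the variable on which the trial was sized.

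**Working it through.** **1. The plan's own figure.** Inputs from Sample Size: difference 35 points, alpha 5%, power 80%, 22 per group, 50 in total. The control rate and sidedness are not stated. I assume a two-sided test. The pooled formula without continuity correction is

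n = [1.96·√(2p̄(1−p̄)) + 0.842·√(p₁(1−p₁)+p₂(1−p₂))]² / 0.35²

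With an assumed 5% versus 40%, p̄ = 0.225:
- 1.96·√0.34875 = 1.157
- 0.842·√0.2875 = 0.451
- n = 1.608² / 0.1225 = 21.1, so 22

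6% versus 41% also gives 22. For dropout, 44/(1−0.12) = 50. The stated size therefore belongs to the binary endpoint. No sample size is given for a continuous one.

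**2. Translating the planned effect to the log scale.** Assume each child's log ratio of follow-up to baseline frequency is normal with the same SD in both arms. A responder is a child whose ratio is at most 0.5. The difference between arms, in SDs of log change, is then z(p_diet) − z(p_control), whatever that SD is.
- 5% versus 40%: −0.253 + 1.645 = 1.392
- 20% versus 55%: 0.126 + 0.842 = 0.968

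The expected test statistic of an analysis of log frequency adjusted for log baseline is about this value times √(22/2) = 3.317.
- 1.392 × 3.317 = 4.62, power about Φ(4.62 − 1.96) = Φ(2.66), above 99%
- 0.968 × 3.317 = 3.21, power about Φ(1.25) = 89%

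These are normal approximations, so they run slightly high at this sample size.

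**3. Simulated power, 22 per arm, calibrated as in step 2.** The documents give no mean, SD or baseline correlation, so all SDs and control rates are assumptions. The wide grid uses control rate 5-20%, SD of log baseline 1.0-2.0 and SD of log change 0.5-1.3. A second set of assumed SDs and control rates was calibrated in the same way.

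| Analysis | Wide grid | Second set | Second set, rounded |
|---|---|---|---|
| t-test, raw follow-up | 3-54% | 9-54% | 10-55% |
| t-test, raw change | 9-79% | 24-78% | 25-80% |
| t-test, percentage change | 57-99% | 67-94% | 65-95% |
| log analysis, baseline-adjusted | 85-99% | 77-99% | 75-99% |

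On the wide grid the responder chi-square has 66-87%.

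**4. One scenario across all tests.** The ranges in step 3 pool different scenarios and partly overlap. With an effect not calibrated to the plan (geometric mean ratio 0.5, SD of log change 1.0, SD of log baseline 1.5, 22 per arm), power is 9% for raw follow-up, 17% for raw change, 45% for percentage change and 62% for the baseline-adjusted log analysis. The order is the same as in step 3, but the levels are lower. The levels depend on the assumptions.

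**The case against.** A reader might infer that the protocol has two competing primary outcomes with two competing tests. The documents do not support that. The abstract and Sample Size agree on the responder proportion, and no continuous primary endpoint, effect size or sample size is defined anywhere. The outcome section lists domains in brackets, and the secondary outcomes there are also domain names. The research question is broad and defines no endpoint. The analysis rule is generic, and applied to the defined primary outcome it gives chi-square. This part of the objection stands.

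A reader might also want one firm power figure for the t-test. None can be had, because the inputs are not in the documents. A t-test on percentage change, the continuous measure closest to the responder definition, does much better than one on raw values. The criticism therefore bears mainly on raw frequency and raw change.

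The covariate list is open, and disease severity could be meant to include baseline seizure frequency. Transformations and final covariates are often left to an analysis plan, which is not shown. That is fair, so the missing covariate alone would be no finding. But the article does not leave the main test open: it fixes an unadjusted t-test for every continuous variable.

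Finally, randomisation takes place midway through the unblinded four-week baseline (Randomization and procedure), so half of the baseline record is made after allocation. This does not argue against adjustment, but it affects which baseline weeks to use.

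**Conclusion.** The point holds in two modest parts.

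- **Label.** The outcome section should state the variable that the abstract and Sample Size already define. This is a matter of clarity and does not put the primary analysis at risk.
- **Test.** For seizure frequency as a continuous variable, the stated unadjusted t-test is inefficient. At the planned effect and 22 per arm, its power on raw follow-up frequency or raw change is roughly 10-55% or 25-80%, against 75-99% for a baseline-adjusted log analysis. With a very wide spread of baseline counts, the raw t-tests fall to 3% and 9%.

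The direction was the same in every set of assumptions tried. The sizes rest on assumed log-normal frequencies, assumed SDs and assumed control rates. The planned chi-square test of the primary outcome is not called into question.

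**What to change.** 1. In the outcome section and its Seizure frequency subsection, name the responder proportion (at least a halving of seizure frequency from baseline) as the sole primary outcome. In the Analyses section, tie it to the chi-square test already planned.
2. Make seizure frequency a named secondary outcome. Analyse it by ANCOVA of log(count + 1) at follow-up on log(baseline count + 1), or by negative binomial regression with log baseline as covariate and recording time as offset. Report a ratio of seizure rates with a 95% confidence interval, in place of Student's t-test.
3. Use the two baseline weeks before randomisation as the baseline covariate, at least in a sensitivity analysis.

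Cost: wording and slightly more analysis work. The seizure calendar is already kept, SPSS fits both models, and the endpoint and sample size do not change. The small downside is that a two-week baseline is a noisier covariate than a four-week one.

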#### Primary outcome

##### Seizure frequency

A seizure calendar is used to record seizures. Types of seizures are described and labelled in accordance with ILAE classification. The number and type of seizures are recorded on the dates they occur.

#### Secondary outcome

##### Seizure severity

The National Hospital Seizure severity scale (NHS3) [26] is a structured interview in which the clinician rater assigns a score to seizure severity based on interference with patient function. Information is gathered from the patient and witnesses, if available. Eight questions are asked about: tonic-clonic movements, falling, injury, incontinence, altered consciousness, postictal impairment, and disruptive automatisms.

##### Side effects

Subjective complaints are assessed using the SIDAED (Side effects of Anti-Epileptic Drug), a list of 46 items with possible anti-epileptic drug-related complaints. The items included in the SIDAED form 10 categories: general Central Nervous System (CNS), behavior (increased irritability), depressive symptoms, changes in cognitive function, motor problems and coordination, visual complaints, headache, cosmetic and dermatological complaints, gastrointestinal complaints, and sexuality and menses. For each item the parents rate the severity of the complaint on a four-point Likert scale (no problem, mild, moderate, or serious problem). In addition, the duration of the complaints is scored (for a few weeks, for months or for a half year or longer).

##### Neurocognitive assessment

*Peabody Picture Vocabulary test*

The Peabody Picture Vocabulary test (PPVT-III-NL: Dutch version) is an individually administered measure of receptive vocabulary [27]. The test can be administered beginning at the age of 2 1/2 years. The child listens to the examiner's stimulus word and must choose the picture that best describes the word from a 4-picture multiple choice array. The score on this test can be interpreted as an achievement test of the child's vocabulary that does not require a verbal response and as a screening measure of verbal ability. There is supportive data for the validity of the PPVT-III as a measure for global cognitive intelligence.

*Beery Developmental Visual-Motor Integration test*

The Beery Developmental test of Visual-Motor Integration (Beery-VMI) is a widely used assessment of psychomotor development. It measures problems with visual perception, motor coordination, and visual motor integration. The 30-item test can be administered from the age of 2 years. The Beery VMI was standardized on a national US sample of 1,737 individuals age 2 to 18 years (2010) and 1,021 adults ages 19-100 (2006), and has proven reliability and validity [28].

*Fepsy computerized test*

The Fepsy is a neurocognitive computerized test battery consisting of different subtests. For this study we use the simple auditory and visual reaction times, in which the stimulus exposure endures until a push-button (space-bar) response is given [29]. Simple reaction tests give information on alertness functions and on the speed at which the information processing system is activated. We also use the binary choice reaction task in which a combination of accuracy and speed of responses are measured. This test measures the speed of central information processing. Finally, we use the finger tapping task in which motor activation and fluency is measured. In general, these tests can be administered from the age of 6.

*Kaufman Assessment Battery*

The Kaufman Assessment Battery for Children II (K-ABC II) is used to investigate the level of information processing capacities of children beginning at the age of 2 1/2 years [30]. Two subtests will be administered: (1) Number recall, which is a measure of sequential processing and short term memory. The examiner says a series of numbers and the child repeats them. Digit span forward is considered a measure of efficiency of attention or "freedom from distractibility" and (2) conceptual thinking, which is a measure of nonverbal reasoning skills. The child looks at pictures and determines the one that does not belong.

*Actigraphy*

During the administration of the PPVT-III and the K-ABCII test, an actigraphic device (Actiwatch^® ^model AW4: Cambridge Neurotechnology Ltd., United Kingdom) will be used to assess motor activity as a measure of alertness. As some of the children in the design are not testable with the described cognitive tests we decided to use an assessment of motor activity in a standardized situation. A wrist watch will be used that translates activity into movement of the watch hand. Registration takes place in a standardized way during the first 10 minutes of the Peabody Picture Vocabulary test and the first 5 minutes of the K-ABC-II test. When patients are not eligible to perform the neurocognitive assessment, the wrist watch will be used for 15 minutes during the visit at the nurse practitioner's office while watching a DVD with songs and pictures.

*SEV Questionnaire*

The SEV questionnaire (Sociaal Emotionele Vragenlijst: Social Emotional Questionnaire) is a DSM-IV oriented questionnaire which is used to assess four domains of behavioral and social emotional dysfunction. These domains are: Attention Deficit Hyperactivity Disorders, Oppositional Defiant behavior and Conduct Disorders, Anxiety and Depression, and Autism spectrum disorders. The questionnaire consists of 72 items describing problem behavior [31].

*SDQ Questionnaire*

The Strengths and Difficulties Questionnaire (SDQ) is a brief behavioral screening questionnaire that provides balanced coverage of children and young people's behaviors, emotions, and relationships [32]. The SDQ is applicable to children beginning at the age of 4 and asks about 25 attributes that are divided into five relevant dimensions: namely conduct problems, emotional symptoms, hyperactivity, peer relationships, and pro-social behavior.

*POMS Questionnaire*

The Profile of Mood States (POMS) has been developed to identify and assess seven transient, fluctuating affective mood states: Tension-Anxiety, Depression-Dejection, Anger-Hostility, Vigour-Activity, Fatigue-Inertia, Friendliness, and Confusion-Bewilderment [33]. The questionnaire contains 65 items. All items describe an emotional state which can be rated on a 5-point scale ranging from "not at all" to "extremely".

*The Personal Adjustment and Role Skills Scale (PARS)*

The Personal Adjustment and Role Skills Scale, 3rd edition (PARS-III) was specifically developed to measure psychosocial adjustment in children with chronic physical illness [34]. This instrument is a brief parent-completed index of youth psychosocial adjustment. The instrument yields six factor-derived psychosocial subscales: namely peer relations, dependency, hostility, productivity, anxiety/depression, and withdrawal. The PARS-III is a reliable and valid index of youth psychosocial adjustment and can be used for both clinical screening and research purposes [35].

*The Hague Restrictions in Childhood Epilepsy Scales (HARCES)*

The HARCES is a questionnaire consisting of 11 items used to assess impairments in daily functioning that are related to epilepsy, e.g. how much influence does the epilepsy have on your child's freedom of functioning in the house? Items are answered on a 4-point scale ranging from "no impairment" to "very much impairment" [36].

##### Credibility And Expectancy questionnaire (CEQ)

The Credibility and Expectancy Questionnaire (CEQ) [37] is a multidimensional self-reported instrument of 6 items, rated on a 9- or 10-point Likert-scale, meant to measure the expectancy and credibility a person has about the therapy he or she will receive. Its sound psychometric properties have been proven. We will measure the credibility and expectancy for the treatment of both the children and their parents.

##### Generic quality of life

*EuroQol*

Living with uncontrolled seizures has a negative impact on the quality of life of the child and his/her parents. Therefore, we will measure generic quality of life of both the children and their parents. For this purpose we will use the EuroQol instrument for children of 12 years and older developed by the EuroQol group [38]. For younger children, we will use a version of the EuroQol developed for children (EuroQol-Youth) or proxies (Wille, 2010). In accordance with the regular EuroQol, the EuroQol-Youth is comprised of the following 5 dimensions: mobility, self-care, usual activities, pain/discomfort and anxiety/depression. Each dimension has 3 levels: no problems, some problems and severe problems, thus defining 243 (3^5^) possible health states. 'Unconscious' and 'dead' have been added to these states, resulting in a total of 245 states. Furthermore, the EQ-5 D consists of a visual analogue scale (VAS) ranging from zero (worst imaginable health state) to 100 (best imaginable health state).

*TAPQOL or TACQOL*

QoL will also be assessed using the TAPQOL (TNO-AZL Preschool Children's Quality of Life) for children aged between 1-5 years [39] and the TACQOL (TNO-AZL Children's Quality of life) for children aged between 6-16 years [40]. There are 12 dimensions in the TAPQOL: lungs, stomach, skin, sleep, appetite, aggressive behavior, positive emotions, fear, vitality, social behavior, motor functioning and communication. All dimensions are scored on a scale from 0-100. The TACQOL is comprised of 7 dimensions: bodily complaints, independence, motor functioning, cognition, social functioning, positive and negative emotions. The scores of the first 5 dimensions vary from 0-32 and the scores of the last two dimensions from 0-16.

